### Study intervention methods

#### TENS

The TENS apparatus (Perfect TENS, TensCare Ltd., Surrey UK) consists of a stimulation unit, a lead wire with two connections, and two circular 25 mm diameter electrode gel pads. The two electrode gel pads are placed bilaterally approximately at the level of the external occipital protuberance (inion) 3–4 cm from the midline where the GON has a more superficial course and where recruitment of neck muscles is avoided. Prior to electrode placement, two areas of the scalp in this site have been closely shaved with an electronic shaver to achieve a better contact surface between the skin and the electrode gel pads.

The stimulation programs used in the TENS trial are pre-set by the manufacturer. The participants can change freely between three different programs, (1) 110Hz/50μs, (2) 10Hz/200μs, and (3) 100Hz/200μs (frequency/pulse width), according to their preference. The usage pattern of the TENS equipment is individual, but participants are encouraged to use the stimulation 30 min twice a day as a minimum, and no more than 12 h in a row to avoid scalp irritation. Patients are advised to use TENS mainly as a preventive treatment, but may freely test if they achieve any abortive effect if using the stimulation during headache attacks.

#### ONS implantation

A cylindrical 8-contact lead (SC-2366–70 Linear 3–6 Percutaneous Lead, Boston Scientific, Marlborough MA, USA) is implanted subcutaneously in the occipital region via a bent 14G Touhy cannula inserted through two incisions over the external occipital protuberance (inion) and behind the mastoid, respectively. The lead is placed transversely approximately one cm above the level of the inion, aiming to cover both the right and left GON. The lead is fixed to the pericranium using an anchor (Injex Bumpy Anchor 97,791, Medtronic, Minneapolis MN, USA), tunneled subcutaneously along the neck, and connected to an IPG (SC-1416 WaveWriter Alpha Prime 16, Boston Scientific) placed subcutaneously in the right infraclavicular region. The implantations are performed as a one-stage sleep/awake procedure with an on-table test stimulation of the implanted lead in order to secure the correct positioning of the lead leading to satisfactory bilateral occipital paresthesia. If necessary, the position of the lead is adjusted based on the participants' verbal feedback on the localization of the evoked paresthesia.

#### Burst ONS

Burst stimulation is a stimulation paradigm devised to mimic the natural firing pattern of neurons by delivering electrical impulses in bursts (short trains separated by a gap). These impulses are delivered in sub-sensory amplitudes resulting in a paresthesia-free stimulation. The parameters for burst ONS (“MicroBurst”, Boston Scientific) are set with an intra-burst frequency of 450 Hz (six pulses), an inter-burst frequency of 40 Hz, and a pulse width of 300 μs [30]. Stimulation amplitude is set to 50% of the detection threshold.

Participants allocated to the burst ONS group receive this stimulation continuously throughout the 12-week blinded trial phase.

#### Placebo

Placebo treatment is performed by leaving the ONS system turned off after the initial programming session throughout the 12-week blinded trial phase.

#### Tonic ONS

In conventional tonic stimulation, the electrical impulses are delivered as regular biphasic square waves. All participants cross over to open-label tonic ONS as the final phase of the trial regardless of allocation group during the blinded part of the trial. A personal remote control allows the participants to change between three different pre-set stimulation programs with frequencies of 10, 30, and 100 Hz, respectively. Pulse width (250–500 µs) and configuration (polarity and activation) of the eight contacts on the linear lead are adjusted to achieve the best possible occipital paresthesia. The participants’ individual perception and comfort thresholds determine the amplitudes and can be controlled using the remote control. The participants are encouraged to use the stimulation continuously but are allowed intermittent use if preferred.

#### Post-procedural care

After ONS implantation, patients are admitted for one night and discharged the following day after a clinical control. To achieve the best possible conditions for programming the ONS system before randomization and blinding, there is a 14-day grace period to ensure the healing of the surgical wounds and reduced tissue swelling. To minimize the risk of postoperative infection, ten days of peroral antibiotics (dicloxacillin 1000 mg three times a day) are prescribed.

### Outcome measures

The response to the different intervention methods is continuously registered by participants filling in a weekly electronic headache registration. Questionnaires on health-related quality of life, self-perceived treatment effect, and symptoms of anxiety and depression prior to every follow-up visit (Fig. 2).

**Fig. 2 Fig2:**
[figure not shown]
Outcome parameters in correlation to trial phases and study visits. TENS, transcutaneous electrical nerve stimulation. ONS, occipital nerve stimulation. PGIC, patient's global impression of change. HADS, hospital anxiety and depression scale. EuroQoL-5D, European Quality of Life – 5 Dimensions

All questionnaires are electronic and are entered via a personal link sent automatically by e-mail. If the headache registrations and questionnaires are not completed within 24 h, an e-mail reminder is generated.

The data collected during each trial phase will be compared to the baseline and analyzed in order to evaluate the study endpoints listed in Table 4.

**Table 4 Tab4:** Study endpoints

**Primary endpoints:**
1. 30% reduction in attack frequency with TENS and ONS
2. Safety in ONS and TENS treatment
**Secondary endpoints**
1. Participant’s assessment of treatment effect evaluated by PGIC-score
2. Treatment efficacy of burst versus tonic ONS as a preventive treatment for chronic cluster headache
3. Feasibility of TENS as a predictor for the outcome of ONS treatment
4. 30% reduction in pain intensity
5. Quality of life as evaluated with the EuroQoL-5D questionnaire
6. Reduction in background headache
7. Self-reported sleep quality
8. Symptoms of anxiety and depression as evaluated by HADS

*TENS* Transcutaneous electrical nerve stimulation, *ONS* Occipital nerve stimulation, *PGIC* Patient's global impression of change, *HADS* Hospital anxiety, and depression scale, *EuroQoL-5D* European Quality of Life – 5 Dimensions

### Headache registration

Participants log information about their headache attacks the past week; number of attacks, mean duration of attacks (in minutes), and severity of attacks on a 0–10 numeric rating scale (NRS, 0 is no pain, 10 is the worst pain imaginable) [31]. In addition, the use of abortive medication and/or oxygen inhalation is registered, as well as the presence of background headache, autonomic facial symptoms, and the participants’ self-reported sleep quality on a four-point Likert scale.

During the TENS- and tonic ONS trial phase, the weekly headache registration will have supplementary questions regarding the use of stimulation; usage pattern (continuous, intermittent, no stimulation), and preferred stimulation program(s).

### Patient’s Global Impression of Change (PGIC)

PGIC is a single, self-administered tool asking respondents to rate how their condition has changed since a certain point in time [32].

In this study, PGIC is used to record the participants’ self-reported perception of the effect of a given treatment (TENS, burst ONS, and tonic ONS) based on a seven-point scale ranging compared to before the treatment was initiated (baseline).

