**Methods:**

An investigator-initiated, double-blinded, randomized, placebo-controlled trial is conducted, including 40 patients with CCH. Eligible patients complete a trial with the following elements: I) four weeks of baseline observation, II) 12 weeks of transcutaneous electrical nerve stimulation (TENS) of the occipital nerves, III) implantation of a full ONS system followed by 2 week grace period, IV) 12 weeks of blinded trial with 1:1 randomization to either placebo (deactivated ONS system) or burst (paresthesia-free) stimulation, and V) 12 weeks of tonic stimulation.

The primary outcomes are the reduction in headache attack frequency with TENS and ONS and treatment safety. Secondary outcomes are treatment efficacy of burst versus tonic ONS, the feasibility of TENS as a predictor for ONS outcome, reduction in headache pain intensity (numeric rating scale), reduction in background headache, the patient’s impression of change (PGIC), health-related quality of life (EuroQoL-5D), self-reported sleep quality, and symptoms of anxiety and depression (Hospital Anxiety and Depression Scale, HADS).

Data on headache attack characteristics are registered weekly. Data on patient-reported outcomes are assessed after each trial phase.

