## Methods: Participants, interventions, and outcomes

### Study design

The study is an investigator-initiated, prospective, double-blinded, randomized, placebo-controlled trial.

After an initial baseline period, all participants are treated with TENS. Following the TENS trial all participants are implanted with an ONS system and randomized into one of two arms; one intervention arm and one placebo arm with an allocation ratio of 1:1. The participants in the intervention arm receive burst ONS (paresthesia-free stimulation). In the placebo group, the ONS system will be left turned off. In the final trial phase, all participants cross over to open-label tonic ONS (Fig. 1).

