### Statistical analysis

Statistical analysis will be conducted by the principal investigator and a statistician blinded for treatment allocation only after follow-up for all participants is completed. No interim analysis will be performed.

Characteristics of the patients will be presented using descriptive statistics to assess if balanced groups were obtained after randomization. The primary analysis will be conducted according to the intention-to-treat principle to avoid introducing bias. In a secondary analysis, a per-protocol analysis will be performed.

The primary outcome is a 30% reduction in attack frequency with TENS and ONS treatment compared to baseline. Relative change in attack frequency (in percent) will be analyzed using the Wilcoxon signed-rank test for paired variables, comparing the baseline data with data from the TENS trial and the trial with burst and tonic ONS, respectively. Because the changes in attack frequency are expectedly skewed [23], a non-parametric test will be applied. In cases with a minimum 30% reduction in attack frequency, sub-analyses will be made to group the treatment responders after relevant cutoffs.

Analysis of the secondary outcomes will be conducted according to the same principle, comparing data from each of the trial phases to baseline using a parametric or non-parametric test for paired variables, depending on the data distribution.

The feasibility of TENS as a predictor for ONS outcome will be evaluated by determining the sensitivity and specificity and calculating the predictive values.

Statistical data analysis will be performed using Stata 17.0 (StataCorp, College Station, USA-TX).

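### PGIC is a change rating, so the paired-to-baseline rule does not fit it and omits burst versus placebo; its reference point for the ONS phases is also unclear

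*Protocol article*

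**What the plan says.** Table 4 lists as secondary endpoint 1: "Participant’s assessment of treatment effect evaluated by PGIC-score".

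The PGIC section describes the instrument as "asking respondents to rate how their condition has changed since a certain point in time". It says the trial uses it for the participant's "perception of the effect of a given treatment (TENS, burst ONS, and tonic ONS" and that the rating is "based on a seven-point scale ranging compared to before the treatment was initiated (baseline".

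On the order of phases, Study design says: "After an initial baseline period, all participants are treated with TENS". The Methods part of the Abstract gives the lengths: 4 weeks of baseline, 12 of TENS, "implantation of a full ONS system followed by 2 week grace period", 12 blinded weeks on burst or a deactivated system, and 12 weeks of tonic stimulation.

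Statistical analysis says: "Analysis of the secondary outcomes will be conducted according to the same principle, comparing data from each of the trial phases to baseline", with a paired parametric or non-parametric test chosen by the data distribution. TENS as a predictor gets its own method (sensitivity, specificity, predictive values). PGIC gets none.

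**The concern.** Two statements about PGIC do not fit the rest of the article.

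- **The test.** A paired test against baseline needs a score at baseline and a score at the end of the phase. PGIC asks how things have changed since a reference point, so no baseline score can exist. The rule is also purely within-participant. For PGIC it names no comparison of burst with placebo, although that is the only contrast protected by randomisation and blinding.
- **The anchor.** The PGIC section treats the moment before the treatment began as the same thing as baseline. This holds for TENS only. Burst starts after TENS, surgery and the grace period, and tonic ONS starts after the blinded phase as well.

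What is at stake is the reading of a patient-perceived outcome. If within-group PGIC scores are reported as the effect of burst or of tonic ONS, change that began under TENS or after surgery may be credited to the later stimulation. The comparison that could support a causal statement about burst would not be among the planned analyses of this endpoint.

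**Working it through.** The article gives no figure for PGIC, so the check compares passages and adds up phase lengths.

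**1. Is there a baseline value to pair?**

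| Instrument | What it records | Baseline collection stated? |
|---|---|---|
| EuroQoL-5D | current state | yes, at baseline and after each later phase |
| HADS | current state | yes, at baseline and after each later phase |
| PGIC | change since a reference point | no, and none is possible |

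The paired rule works for the first two and cannot be applied literally to the third. The nearest substitute pairs each score with the constant for no change. That is the same as a one-sample signed-rank test. With ten illustrative scores (1, 2, 2, 3, 3, 4, 5, 2, 1, 3; no change taken as 4), both forms give a statistic of 2.5 and p = 0.0195. A test is therefore available, but it is not the one written, and it remains a within-group test that says nothing about burst against placebo.

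**2. What period does the rating cover?**

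Inputs from the Abstract: TENS 12 weeks, grace period 2, blinded phase 12, tonic phase 12. The wait for surgery is not stated and would lengthen the totals, hence ≥.

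| Rating at end of | Anchor = pre-TENS baseline | Anchor = start of that phase |
|---|---|---|
| TENS | 12 weeks | 12 weeks |
| Blinded phase | 12 + 2 + 12 ≥ 26 weeks | 12 weeks (2 + 12 = 14 from implantation) |
| Tonic ONS | 26 + 12 ≥ 38 weeks | 12 weeks |

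Under the pre-TENS anchor, the phase being rated fills at most 12/26 = 46% of the span at the end of the blinded phase and at most 12/38 = 32% at the end of tonic ONS. The tonic rating also takes in the preceding blinded phase, which was burst for one arm and off for the other. Under the phase-start anchor these overlaps largely disappear.

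**3. Which anchor does the article mean?**

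Study design, the Abstract and the EuroQoL-5D and HADS sections all use baseline for the initial period before TENS, and Outcome measures says data from each phase are compared with it. This favours the pre-TENS reading. The wording about a given treatment and the time before it began allows the start of each phase. The two readings give different questionnaires, and the article does not settle between them.

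**4. Does the anchor bias burst versus placebo?**

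No. Both arms go through TENS, implantation and the grace period before allocation, and both use the same reference point. Earlier change is common to the arms by design, so a between-arm comparison at the end of the blinded phase is valid under either reading.

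**The case against.** The best reply has five parts.

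- **The anchor is ambiguous rather than fixed wrongly.** This stands. The sentence is visibly garbled and the item shown to participants is not available. The 26- and 38-week spans hold only under the pre-TENS reading.
- **A common baseline is the declared design for every outcome.** This stands as well. A reader might infer that PGIC does not measure the treatment it names, or that the long anchor hides the effect of burst. The documents support neither. The shared anchor keeps the randomised contrast valid, and nothing in the article quantifies a loss of sensitivity. What remains is that within-group ONS ratings, above all for tonic, do not isolate the phase.
- **The endpoint can still be analysed, and detail belongs in the SAP.** A reader might infer that endpoint 1 cannot be analysed at all. That goes too far, since a one-sample or between-arm test is easy to run and an SAP may specify one. But the point does not rest on missing detail. The article states a rule, sets TENS prediction apart from it, and leaves PGIC under a rule that does not apply.
- **Placebo participants are asked too.** The PGIC section names burst but not placebo, and a reader might infer that the placebo arm is left out. Outcome measures places questionnaires on self-perceived effect before every follow-up visit without restriction by arm, and the Abstract has patient-reported data collected after each phase. The schedule figure is not shown. This is a wording gap only.
- **Re-anchoring could do harm.** Anchoring tonic PGIC to the end of the blinded phase would give former burst and former placebo participants different reference states. A burst responder who stays well could score no change, while a former placebo participant could score a large gain. This stands, and it argues against changing the item.

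**Conclusion.** The point holds for the stated analysis and, more narrowly, for the anchor. The paired-to-baseline rule is wrong for PGIC because a change rating has no baseline value, and it omits burst versus placebo. This follows from the article's own description of the instrument and needs no assumption.

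The anchor is unclear for both ONS phases. Assuming the pre-TENS baseline and no wait for surgery, within-group ratings span 26 and 38 weeks, of which 12 belong to the named phase; any wait makes the spans longer. Assuming a phase-start anchor, the spans are about 12 weeks and the attribution problem largely goes away. Under both assumptions the randomised contrast is sound.

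The consequence is limited to one secondary endpoint. It is worth correcting because an analysis plan can repair the test but cannot recover which moment participants were asked to compare with.

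**What to change.** In Statistical analysis:

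- Exempt PGIC from the paired-to-baseline rule.
- Compare its seven ordered categories at the end of the blinded phase between burst and placebo, by a rank-sum test or ordinal logistic regression.
- Report PGIC after TENS and after tonic ONS as category distributions, without attributing them to that phase alone.

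In the PGIC section:

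- State, for each phase, the reference point actually used in the questionnaire.
- Say that PGIC covers both arms of the blinded phase.
- Do not re-anchor the item for participants already enrolled. Recruitment began in September 2021 and was expected to end in late 2023, so a change would split 20 per arm by anchor.

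The cost is a few sentences and no new data. The article plans no interim analysis and none until all follow-up is complete, so the analysis text can be corrected before any result is known.

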### European Quality of Life – 5 Dimensions (EuroQoL-5D)

EuroQoL-5D is a standardized tool for examining the health-related quality of life, and consists of a descriptive part with five questions about mobility, personal care, usual activities, pain, and anxiety/depression. In addition, the questionnaire also contains the EQ-VAS (visual analog scale), which measures the participant's self-assessed state of health on a 0–100 scale from "worst imaginable" to "best imaginable" [33].

In this study, the participants fill out the EuroQoL-5D questionnaire at the end of each trial phase (baseline, TENS trial, blinded trial, and tonic ONS trial).

### The Hospital Anxiety and Depression Scale (HADS)

A simple, validated tool for evaluating patients' risk of anxiety and/or depression primarily focusing on non-physical symptoms [34]. The questionnaire comprises seven questions for depression (HADS-D subscale) and seven questions for anxiety (HADS-A subscale). Scoring for each item ranges from zero to three, with a total subscale score of ≥ 8 points out of a possible 21 denoting considerable symptoms of anxiety or depression. HADS is useful both for screening and for monitoring the progression or resolution of psychological symptoms.

In this study, the participants fill out the HADS questionnaire at the end of each trial phase (baseline, TENS trial, blinded trial, and tonic ONS trial).

### Participant information

All participants sign an informed consent before enrolment and are given both oral and written information before consenting. This includes information about the purpose of the project, potential risks and side effects, and the right to terminate the trial at any given time without consequences for present or future medical treatment. It is ensured that the participants fully understand the information given by the principal investigator at the Department of Neurosurgery, Aarhus University Hospital, or site investigators at the Danish Headache Centre. Participants are encouraged to bring a next of kin to the consultation.

Before enrolling the participants are informed of, and consent to, the fact that they are blinded to the type of treatment they receive in the randomized trial phase.

The written information is published as a pamphlet explaining all information in Danish layman’s language. The content and wording of the written participant information are approved by the Central Denmark Region Committee on Health Research Ethics.

The pamphlet will clearly state the potential risks and side effects of all procedures involved in the study.TENS: Perceptible occipital paresthesia during stimulation. Risk of irritation of the skin covered by the gel electrodes.ONS-implantation: Risk of infection and hematoma. Lesion of nerve trunks and blood vessels during placement and tunneling of the lead. Risk of pneumothorax when tunneling the lead. Post-operative pain.ONS treatment: Perceptible occipital paresthesia during tonic stimulation. Pain and/or discomfort at IPG site. Risk of lead migration or fracture. Preterm battery depletion.

### Sample size

Based on our previous experience with ONS treatment [26], we estimate that 50% of the participants who receive active treatment with burst ONS will reach the primary endpoint of a 30% reduction in attack frequency. A blinded trial with burst ONS and placebo has to our knowledge not been carried out earlier, but we hypothesize that no more than 10% in the placebo group will meet the primary endpoint [35]. The sample size is calculated using Fisher’s Exact test based on the above-mentioned assumptions and with 80% power (two-tailed) and a α = 0.05, a total of 40 participants (20 in each allocation group) are needed to be enrolled in the study and an ONS-system implanted.

Each enrolled participant contributes their data regardless of whether they complete the project or not. In case of participants excluded after enrollment, the reason for exclusion will be described.

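### Two-sided Fisher's exact test with 20 per arm gives 74.2% power at 50% v 10%, not the stated 80%; separately, the article uses full-scale attack counts only within participants

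*Protocol article*

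**What the plan says.** Under Sample size, the protocol article writes "we estimate that 50% of the participants who receive active treatment with burst ONS will reach the primary endpoint of a 30% reduction in attack" rate, and supposes that "no more than 10% in the placebo group will meet the primary endpoint". It then says: "The sample size is calculated using Fisher’s Exact test", with "80% power (two-tailed) and a α = 0.05", and arrives at 40 participants, 20 per group. No allowance for dropout is stated.

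Table 4 gives the first primary endpoint as "30% reduction in attack frequency with TENS and ONS". The data beneath it are finer. Under Headache registration, "Participants log information about their headache attacks the past week; number of attacks" is the first item of a weekly log. The Abstract gives 4 weeks of baseline and 12 weeks of blinded treatment.

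The Statistical analysis section treats relative change in attack frequency as a percentage, without a cut, by Wilcoxon signed-rank tests of each active phase (TENS, burst, tonic) against baseline. Responder groupings appear there as sub-analyses. The section names no test of burst against placebo; Fisher's test appears only under Sample size.

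**The concern.** There are two separate problems.

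1. **The power figure.** The stated test, rates, alpha and group size do not give the stated power. A reader who relies on 80% takes the risk of missing a true effect of the planned size as one in five, when it is about one in four.

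2. **The outcome scale of the randomised contrast.** Sixteen weekly counts per participant are reduced to one yes/no for the only between-arm comparison that is sized. A 31% and a 100% reduction count the same, as do a 29% reduction and a doubling. The article does use the full scale, but only for change from baseline within participants, which does not compare burst with placebo.

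All 40 participants have a device implanted and the number is small, so information given up in the randomised contrast is hard to replace by enrolling more.

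**Working it through.** **Inputs, all from Sample size:** p1 = 0.50, p2 = 0.10, n = 20 per arm, two-sided alpha 0.05, Fisher's exact test, no dropout.

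**Where 40 comes from.** Pooled chi-square formula without continuity correction:

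n = [1.960·√(2·0.30·0.70) + 0.842·√(0.50·0.50 + 0.10·0.90)]² / 0.40²
= [1.270 + 0.491]² / 0.16 = 3.101 / 0.16 = 19.4, so 20 per arm.

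The formula power at 20 is Φ[(0.40·√20 − 1.270)/0.583] = Φ(0.889) = 81.3%. Other standard two-sided formulas give other sizes: unpooled 17, arcsine 19, continuity-corrected 25.

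**Fisher at 20 per arm.** For each number of placebo responders b, find the smallest number of burst responders a with two-sided p ≤ 0.05. Then sum P(b)·P(A ≥ a), with B ~ Bin(20, 0.1) and A ~ Bin(20, 0.5).

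| b | smallest a | p | P(b) | P(A ≥ a) | product |
|---|---|---|---|---|---|
| 0 | 5 | 0.047 | 0.1216 | 0.9941 | 0.1209 |
| 1 | 7 | 0.044 | 0.2702 | 0.9423 | 0.2546 |
| 2 | 9 | 0.031 | 0.2852 | 0.7483 | 0.2134 |
| 3 | 10 | 0.041 | 0.1901 | 0.5881 | 0.1118 |
| 4 | 11 | 0.048 | 0.0898 | 0.4119 | 0.0370 |
| 5 | 13 | 0.025 | 0.0319 | 0.1316 | 0.0042 |
| 6 or more | | | | | 0.0006 |

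The total is 0.742, which is 5.8 points below 80%. Doubling the one-sided p-value gives the same result. Fisher's power is 78.6% at 22 per arm and 81.1% at 23, so 46 participants are needed. With losses it is 70.9% at 19 per arm and 66.8% at 18. Pearson's uncorrected chi-square on the same responder endpoint has 83.8% power by enumeration at 20 per arm, with a largest type I error of about 5.3%. With 10% responders in both arms, Fisher rejects only 1.2% of the time.

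**What the cut may forgo.** The documents give no SD, dispersion or attack distribution, so everything here is assumed.

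- *Simple bound.* If change is normal with a common shift, 50% v 10% at the cut is a difference of 0 − (−1.28) = 1.28 SD. The two-sample t-test then has noncentrality 1.28·√10 = 4.05 and power 97.7%.
- *Simulated counts, common shift.* Responders were held near 50% v 10%, with 4 baseline and 12 follow-up weeks and a log-ratio SD of 0.2 to 0.8. Fisher on the cut gave 0.73 to 0.75, and ANCOVA of log count on arm and log baseline gave 0.97 to 0.98. The gain is about 23 to 25 points. Holding placebo at 10% required its median rate ratio to rise from 1.04 at the smallest spread to 2.15 at the largest.
- *Simulated counts, responder mixture.* 44% to 72% of the burst arm had a true reduction of 45% to 90%. Fisher gave 0.72 to 0.76 and ANCOVA 0.85 to 0.97, a gain of about 10 to 22 points. A rank-sum test on percent change gave 0.69 to 0.88, from about 6 points below Fisher to about 14 above.
- *Where it reverses.* Responders were about 50% v 11 to 13%, and 5% of both arms nearly remitted. With a 97% reduction in those participants, Fisher gave 0.67 and log-rate ANCOVA with 0.5 added to counts gave 0.38; with a 90% reduction, 0.66 and 0.50. When burst non-responders instead worsened somewhat, the figures were 0.66 v 0.59 and 0.67 v 0.46. A further near-remitter run with placebo response of about 17 to 20% showed a smaller loss, about 7 points.

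**The case against.** The strongest reply has four parts.

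- **Fisher is a sizing test here.** The article does not say burst and placebo will be compared by it, although a reader might infer that. The analysis section leaves percent change uncut, and a between-arm model may stand in the full protocol or SAP, neither of which is shown. This stands: the point is confined to what the article sizes and what it states, and the lack of a named between-arm test is not itself counted as an error.
- **The cut did not cause the shortfall.** The 80% was set for the responder endpoint, and the same endpoint under uncorrected chi-square exceeds 80% at 20 per arm. This also stands. A reader might infer that dichotomising took the trial below its target, but the power error is a mismatch between formula and test.
- **The gain depends on the scenario.** A few near-zero counts become outliers on a log scale and inflate the residual variance, while a responder cut is not affected. Table 2 admits patients with remissions shorter than three months, close to the length of the blinded phase, so near-remission is plausible. This stands as a limit on size: no fixed gain can be claimed, and no single log model is best everywhere.
- **A 30% reduction is the declared clinical endpoint, supported by cited sources, and a risk difference also has a confidence interval.** True, and a reason to keep the responder result. It does not correct the power figure or put the weekly counts to use in the randomised contrast.

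**Conclusion.** The concern holds in two parts of different strength.

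The power statement is wrong as written: 74.2% instead of 80%. This is exact, rests only on the article's own inputs and assumes no dropout.

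The second part is a judgement on efficiency. The article confines the full-scale outcome to paired tests and sizes the randomised contrast only on the 30% cut. A baseline-adjusted count analysis would usually gain about 10 to 25 points at 20 per arm, if responders are near 50% v 10% and either a common shift or a plain responder mixture applies. It could lose power, by about 7 to 29 points in the runs described, if a few participants in both arms nearly remit or burst non-responders worsen. The documents cannot settle which case applies. The finding is worth acting on before unblinding, but it does not show the responder endpoint to be invalid.

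**What to change.** 1. Under Sample size, restate the power as about 74% for two-sided Fisher's exact test with 20 per arm at 50% v 10%, or name the test that does give 80%, such as the uncorrected chi-square. This is a change of wording.

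2. Before unblinding, specify in the protocol or SAP a between-arm, baseline-adjusted comparison of attack rate over the 12-week blinded phase. One option is a negative binomial or log-rate model with log baseline rate as covariate and a permutation p-value, with the handling of near-zero counts fixed in advance. Report the rate ratio with its 95% CI.

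3. Keep the 30% responder proportion per arm beside it, with the risk difference and CI. Give the power of the count analysis under stated assumptions, including a near-remission case.

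No new data, visits or participants are needed, and the article says analysis waits until all follow-up is complete, with no interim look. The cost is that the headline becomes a rate ratio, which is less direct for clinicians than a responder proportion, and that the model is sensitive to near-remitters.
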